## Abstract

**Background:**

Currently, the treatment of cognitive dysfunction after acute traumatic brain injury (TBI) remains a challenge, and novel therapeutic methods are urgently needed. Median nerve stimulation (MNS) is a noninvasive neuromodulation technique that has recently shown positive effects in promoting recovery from coma after acute brain injury. It has been shown to improve cognition in healthy volunteers, and may be a potential therapeutic approach for cognitive dysfunction in patients with acute TBI.

**Objective:**

The primary aim of this study is to evaluate the feasibility, safety, and preliminary efficacy of MNS for cognitive dysfunction in patients with acute TBI.

**Methods:**

This study is designed as a prospective, single-center, assessor-blinded, sham-controlled, randomized pilot study. Thirty adult patients with cognitive dysfunction after TBI will be enrolled and randomized to either the stimulation or sham group in a 1:1 allocation ratio. In the stimulation group, MNS is performed on the right wrist (40 Hz, pulse width 300 µs, 20 s on/40 s off, 8 hours per day). The sham group will receive stimulation using an identical device set to deliver 0 mA. Feasibility, safety, and preliminary efficacy will be evaluated at 1 and 3 months after the injury. Feasibility and acceptability will be assessed via recruitment, adherence, retention, and participant-reported acceptability using Likert scales. These measures will be summarized descriptively, and completion rates will be calculated and reported. Safety will be primarily assessed by ascertainment of adverse events from enrollment to 3 months. Further safety assessment will examine side effects using a Likert questionnaire and the impact on peripheral hemodynamic responses. Additionally, the potential efficacy of MNS on cognitive dysfunction will be assessed using multiple cognitive scales; neuroradiological tests, including magnetic resonance imaging and magnetoencephalography; and cognitive-related serum biomarkers.

**Results:**

Ethics approval was obtained in January 2025, and the trial was registered on ClinicalTrials.gov in February 2026. Participant recruitment is scheduled to begin in July 2026, with completion anticipated in June 2027. Data analysis will commence after completion of follow-up assessments, and study findings are expected to be published in late 2027.

**Conclusions:**

This pilot trial will provide preliminary evidence on the feasibility and safety of MNS as a novel intervention for cognitive dysfunction after acute TBI. The results will guide the development of larger-scale trials and optimization of study design.

## Introduction

Traumatic brain injury (TBI), a leading cause of death and disability, is a significant global public health problem [1,2]. It can cause cognitive dysfunctions, including executive function, memory, attention, language, and visuospatial function, which seriously affects patients’ quality of life and places a substantial burden on families and society [3]. Currently, the main therapeutic methods for cognitive impairment include cognitive training, drug therapy, hyperbaric oxygen therapy, and aerobic exercise therapy [4-7]. These approaches have shown potential benefits for cognitive impairment. However, the improvement in overall cognitive function is inconsistent. Moreover, all the interventions are usually performed during the chronic stage of TBI, leading to often delayed and suboptimal therapeutic outcomes [8]. Thus, treatment options for cognitive impairment during the acute stage of TBI remain limited.

Recently, noninvasive neuromodulation techniques, including repetitive transcranial magnetic stimulation (TMS), transcranial direct current stimulation (tDCS), transcutaneous auricular vagus nerve stimulation, and median nerve stimulation (MNS), have been recognized as having promising potential in improving cognitive function in patients with cognitive impairment caused by stroke, intracerebral hemorrhage, and TBI [9-12]. Among these techniques, MNS is a simple, inexpensive, and noninvasive neuromodulation technique that has been shown to improve recovery after TBI and to hasten awakening from coma, as demonstrated in our previous study [13]. Furthermore, clinical studies have shown that it can effectively improve cognitive function in healthy individuals and enhance cognitive recovery following stroke [14]. Emerging preclinical evidence further suggests that MNS may exert neuroprotective effects after TBI by attenuating oxidative stress and ferroptosis, activating the nuclear factor erythroid 2-related factor 2 or glutathione peroxidase 4 signaling pathway, and promoting the expression of proteins associated with neuronal survival and synaptic plasticity [15]. These findings provide a plausible biological mechanism through which MNS may facilitate cognitive recovery during the early postinjury period. As the acute phase following TBI represents a critical window of enhanced neuroplasticity, initiating neuromodulatory interventions during this stage may maximize their therapeutic potential.

Despite these promising findings, clinical evidence regarding the use of MNS for cognitive dysfunction during the acute stage of TBI remains lacking. To our knowledge, no randomized controlled trial (RCT) has evaluated the feasibility, safety, or preliminary efficacy of MNS in this population. Therefore, we designed this pilot RCT to evaluate the feasibility and safety of MNS and to explore its preliminary effects on cognitive dysfunction in patients with acute TBI. In addition, serum biomarkers and magnetoencephalography (MEG) will be assessed to provide preliminary insights into the potential biological mechanisms underlying the effects of MNS. The findings of this pilot study will inform the design of a future definitive RCT.

## Methods

### Study Design

This study is a prospective, single-center, assessor-blinded, sham-controlled, randomized pilot study. The study protocol was developed in accordance with the Consolidated Standards of Reporting Trials (CONSORT) extension for pilot and feasibility trials [16]. The CONSORT flow diagram is presented in Figure 1. Thirty patients with TBI and cognitive dysfunction will be enrolled and randomly allocated to an active or sham MNS group.

### Ethical Considerations

This trial was approved by the ethics commission of Beijing Tiantan Hospital, Capital Medical University (KY2024-409-02), on January 27, 2025, and is registered on ClinicalTrials.gov (NCT07413562). The accepted version of the study protocol is 3.0. The study was designed according to Good Clinical Practice, the principles of the Declaration of Helsinki, and standards for professional conduct. Written informed consent will be obtained from all participants prior to enrollment in accordance with the Declaration of Helsinki and its later amendments [17]. The results of this randomized pilot study will be disseminated via peer-reviewed publications and congress presentations. This present protocol was written based on the Standard Protocol Items for Clinical Trials.

**Figure 1. F1:**
[figure not shown]
Consolidated Standards of Reporting Trials (CONSORT) flow diagram. MEG: magnetoencephalography; MNS: median nerve stimulation; MRI: magnetic resonance imaging.

### Participants

Patients with cognitive dysfunction after acute TBI will be asked to join the study at the Department of Neurotrauma, Beijing Tiantan Hospital. Participants will be randomly allocated in a 1:1 ratio to either the active MNS group or the sham group.

### Eligibility Criteria

The inclusion and exclusion criteria are summarized in Textbox 1.

Textbox 1.Inclusion and exclusion criteria.
**Inclusion criteria**
Aged 18-64 yearsAdmitted within 3 days after injury with a Glasgow Coma Scale score of 9 to 12 at admission and imaging abnormalities consistent with traumatic brain injury (TBI)Presence of cognitive dysfunction assessed within 1 week after injury, defined as a Mini-Mental State Examination score ≤26Preinjury Clinical Dementia Rating score of 0, as reported by family membersPreinjury education ≥6 years and able to understand instructions and cooperate with cognitive assessments, magnetic resonance imaging (MRI), and magnetoencephalography (MEG) examinations
**Exclusion criteria**
Requirement for emergent neurosurgical intervention during treatment, including surgery, intracranial pressure monitoring device placement, or drainage catheter insertionUnstable vital signs or hemodynamics, or unstable cardiac, pulmonary, hepatic, renal, or hematopoietic disordersPreexisting central nervous system disorders associated with cognitive decline, including previous TBI, intracranial infection, brain tumor, epilepsy, stroke, neurodegenerative diseases, carbon monoxide poisoning, or alcohol abuseInability to complete assessments because of severe visual or hearing impairment, severe psychiatric or behavioral disorders, contraindications to MRI, or intolerance to MEGShort life expectancy due to critical illnessExtensive skin lesions or scars on the right forearm, right median nerve injury, brachial plexus injury, cervical spinal cord injury, or intolerance to median nerve stimulationPregnancy or lactationParticipation in another ongoing clinical trial

The withdrawal criteria include (1) occurrence of any exclusion criterion, (2) occurrence of severe safety events, (3) poor compliance and difficulty in carrying out the trial, and (4) withdrawal of consent.

### Recruitment

Patients who are hospitalized in the Department of Neurotrauma, Beijing Tiantan Hospital, will consent to be screened for the study. A member of the research team will screen eligibility according to the criteria and take a brief medical history. The results of all screenings will be recorded both in the patients’ medical notes and on the study case report form (CRF). The potential participants will be carefully assessed for cognitive functions using the Mini-Mental State Examination (MMSE). Before enrollment, the treating investigator will assess each potential participant’s capacity to provide informed consent based on their ability to understand the study information, appreciate its implications, communicate a choice, and provide informed agreement. Participants judged to have adequate decision-making capacity will provide written informed consent themselves. If a participant is considered unable to provide valid informed consent, written informed consent will be obtained from a legally authorized representative in accordance with institutional ethics requirements. The researchers involved in the trial will be responsible for recruiting participants who have consented to participate and who meet the established inclusion criteria.

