### Study Plan

Patients with TBI are routinely screened on the seventh day after injury. If cognitive dysfunction is detected, the patient may be eligible to participate according to the inclusion and exclusion criteria. Eligible patients will be informed about the study and provided with an information leaflet. If the patient is willing to participate, an appointment will be scheduled.

#### Visit 1

At the initial visit, which will be the seventh day after injury, written informed consent will be confirmed, and the participant will then be allocated to a group. Demographic data and results of neurological examinations will be collected. Neurological function, cognitive function (via scales, MEG, and serum biomarkers), mental behavior, activity of daily living, and quality of life will be assessed. Afterward, the participant will receive a median nerve stimulator and will receive brief training and instructions. Then the stimulation phase for 2 weeks starts. The treatment will be performed in the hospital under the supervision of trained study staff. The participant is advised to contact the principal investigator during interventions if any side effects occur.

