### Outcomes

#### Primary Outcome

##### Feasibility

Referring to the previous recommendations, the feasibility of this pilot study will be evaluated based on the following measures: (1) enrollment rate—the proportion of participants who meet the eligibility criteria and provide consent after baseline screening; (2) recruitment rate—the mean number of participants enrolled in the study per month; (3) adherence rate—the proportion of completed scheduled stimulation hours, which will be used to assess the acceptability of the interventions; and (4) retention rate—the proportion of participants who complete all outcome measurements from the baseline to follow-up assessments [15,18]. These measures will determine whether to proceed with a future main trial.

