### Progression Criteria

The primary purpose of this pilot study is to determine whether a future definitive RCT is feasible. Progression to a full-scale RCT will be guided by predefined feasibility and safety criteria rather than exploratory efficacy outcomes. Specifically, progression will be considered feasible if the following criteria are met: (1) an enrollment rate of at least 60% among eligible patients; (2) a recruitment rate of at least 2 participants per month; (3) an adherence rate of at least 80% of the prescribed stimulation sessions; (4) a retention rate of at least 80% at the 3-month follow-up; (5) no unexpected serious device-related AEs attributable to the intervention; and (6) acceptable participant satisfaction with the intervention, defined as a median score of ≥4 on the 5-point Likert acceptability questionnaire. If one or more of these criteria are not achieved, the feasibility findings will be carefully reviewed to identify barriers and determine whether modifications to the study design, intervention protocol, recruitment strategy, or outcome assessments are required before proceeding to a future definitive RCT. Exploratory efficacy outcomes will be used to estimate treatment effects and variability to inform the sample size calculation and design of the subsequent trial, but they will not determine progression to the definitive study.

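### The Recruitment section takes consent before screening, while the Study Plan and Table 1 screen first; under the Recruitment order, patients who decline screening leave the enrollment-rate denominator and bias the rate upward

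*Protocol article*

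**What the plan says.** **Order of events.** Recruitment opens with "Patients who are hospitalized in the Department of Neurotrauma, Beijing Tiantan Hospital, will consent to be screened for the study". The eligibility check, brief history and MMSE follow. The same section then describes a second step: "Before enrollment, the treating investigator will assess each potential participant’s capacity to provide informed consent", with written consent from the patient or a legally authorized representative.

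Study Plan starts elsewhere: "Patients with TBI are routinely screened on the seventh day after injury". A patient in whom cognitive dysfunction is found may be eligible, and then "Eligible patients will be informed about the study and provided with an information leaflet". At Visit 1, on day 7, "written informed consent will be confirmed, and the participant will then be allocated to a group". Table 1 agrees with this order: the eligibility screen is in the enrollment column and informed consent is in the day-7 allocation column.

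**The outcome that depends on it.** Enrollment rate is the first primary feasibility measure, defined under Feasibility as "the proportion of participants who meet the eligibility criteria and provide consent after baseline screening". Progression Criteria sets the first threshold as "an enrollment rate of at least 60% among eligible patients". The article does not say how a patient who declines screening is counted.

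**The concern.** If only patients already found eligible are told about the trial, nobody can have agreed beforehand to be screened for it. So the two sections describe different first contacts with the patient.

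The difference reaches criterion 1 through its denominator. Under the Study Plan order, an unwilling patient is found eligible, declines, and counts as an eligible patient who did not enroll. Under the Recruitment order, the same patient may decline at the screening step. Eligibility is then never established, and the patient is not among the eligible.

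The enrollment rate would then partly measure agreement among people who had already agreed once. It would overstate the uptake that a definitive trial should expect, and the pilot could meet its first criterion when acceptance among all suitable patients was below 60%.

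**Working it through.** **Inputs from the article.** Threshold 60% among eligible patients (Progression Criteria). Total sample size 30, that is 15 per group × 2 (Sample Size). The 60% is a chosen cut-off, so there is no calculated figure to reproduce.

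**Inputs that are assumptions.** The article gives neither of these:
- A, the true acceptance among all patients who would be eligible: taken as 30% to 50%.
- s, the share of refusals made at the screening step: taken as 0 to 100%.

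**Step 1. Observed rate.** Of all patients who would be eligible, a fraction (1 − A) × s declines screening and is never classified. The rest form the recorded denominator, so

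observed rate = A / [1 − (1 − A) × s].

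At s = 0 this equals A. It rises with s, so the bias has one direction.

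| A | s = 0 | s = 0.25 | s = 0.5 | s = 0.75 | s = 1 |
|---|---|---|---|---|---|
| 30% | 30% | 36% | 46% | 63% | 100% |
| 40% | 40% | 47% | 57% | 73% | 100% |
| 50% | 50% | 57% | 67% | 80% | 100% |

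Example: A = 40%, s = 0.5 gives 0.40 / (1 − 0.60 × 0.5) = 0.40 / 0.70 = 57%.

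**Step 2. Where a fail becomes a pass.** Setting the observed rate to 0.60 gives s = (1 − A/0.60) / (1 − A).
- A = 30%: 0.500 / 0.70 = 71%
- A = 40%: 0.333 / 0.60 = 56%
- A = 50%: 0.167 / 0.50 = 33%

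In patients, for A = 40%: 75 would be eligible, 30 enroll and 45 refuse. If 25 of the 45 (56%) decline at screening, the recorded rate is 30 / (75 − 25) = 30/50 = 60%, against a true 30/75 = 40%.

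**Step 3. What the criterion does when nobody is lost at screening.** With 30 enrolled, 60% means at most 30 / 0.60 = 50 eligible patients. The binomial chance that at least 30 of 50 enroll is 0.3% at a true rate of 40%, 10% at 50%, 56% at 60% and 99.97% at 80%. The criterion therefore separates poor from good uptake when every refusal falls after screening.

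With A = 40% and s = 0.5, acceptance among those recorded as eligible is 57%. That lies between 50% and 60%, so the chance of passing with 50 recorded eligible patients lies between 10% and 56%, instead of 0.3%. Even where the expected rate still fails, the protection is weaker.

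**The case against.** A reader might infer that under the Recruitment order refusers never become eligible at all, so that criterion 1 passes almost automatically. The article does not support this. The Recruitment section has two steps, and its written consent to the trial comes after the eligibility check and MMSE. A patient who passes screening and then refuses is eligible, not enrolled, and stays in the denominator. The Feasibility definition also ties the rate to consent given after baseline screening. A rate of 100% needs every refusal to fall at the first step, and nothing in the article says so. Intermediate splits can still fail, as the 57% shows.

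It can also be said that the routine day-7 screening is ordinary cognitive testing on the ward, ahead of the study's own eligibility check. That softens the conflict. It does not remove it, because the Study Plan still informs only patients already found eligible.

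The recruitment criterion of at least 2 participants per month is a partial safeguard, since refusal at any step lowers that count. It is an absolute count, however. A large pool of suitable patients could meet it with low acceptance.

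Finally, how decliners are logged is a detail that an article may leave to the full protocol, and the CONSORT diagram is not shown. That is fair, and the missing log entry is not the point here. Two conflicting orders in the published text are.

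**Conclusion.** The point holds as a conflict between sections that can bias a primary feasibility outcome upward. The Recruitment section is out of line with the Study Plan and Table 1, and its order removes screening decliners from the denominator of criterion 1.

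The size cannot be fixed from the article. It rests on the assumed A and s. At 40% true acceptance the observed rate runs from 40% (s = 0) through 57% (s = 0.5), and crosses 60% at s of about 56%. At 50% true acceptance, one third of refusals at the screening step is enough.

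It would go too far to say that the criterion loses its power to stop or modify the programme. Refusals after screening still count, the monthly recruitment criterion still responds to poor uptake, and missing any single criterion leads to review. This should be settled before recruitment starts, because decliners who were not logged cannot be recovered later.

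**What to change.** 1. Reconcile Recruitment and Study Plan to one order that matches the Feasibility definition and Table 1: eligibility is established first, then information and consent. Remove the consent-to-screening wording from Recruitment.
2. If a separate consent to screening is kept, say so in both sections and log every patient who declines it.
3. In that case report criterion 1 in two ways: enrolled / eligible, and a lower bound, enrolled / (eligible + decliners not excluded by criteria readable from the clinical record).

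The second figure should stay a bound and not replace the main rate. The family-reported preinjury Clinical Dementia Rating, the MMSE and the ability to cooperate with MEG may not be in the record. Some decliners kept in the bound would therefore be ineligible, and it would understate the rate.

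Cost: a wording change in two sections and, if step 2 applies, a short log entry per decliner. The existing record of screening results does not cover people who were never screened, and the use of decliners' records would need to fit the ethics approval. The reported enrollment rate may be less favourable.

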### Randomization

Once written informed consent has been obtained and eligibility has been confirmed, participants will be randomly assigned in a 1:1 ratio to either the active MNS group or the sham group. An independent investigator who is not involved in participant recruitment, intervention delivery, outcome assessment, or data analysis will generate the allocation sequence using an online computer-based randomization program. Randomization will be performed using a permuted block design with variable block sizes to ensure allocation concealment. No stratification factors will be applied. The allocation sequence will be securely maintained within the online randomization system and will remain inaccessible to the clinical investigators before randomization. After completion of the baseline assessment and confirmation of participant eligibility, the independent investigator will release the randomization code through the online system, and the participant will then be assigned to the corresponding treatment group. Clinical investigators cannot influence the randomization process.

### Interventions

Participants will receive right MNS (active or sham) for 2 consecutive weeks in addition to standard care. During the intervention period, medications that may affect cognitive function will not be permitted. The median nerve stimulator (XCH-B1; Jiangxi Nuocheng Electric Co Ltd) delivers asymmetric biphasic pulses. In the active MNS group, stimulation will be delivered at a fixed frequency of 40 Hz with a pulse width of 300 µs using a 20-second ON or 40-second OFF duty cycle. During the first treatment session, the treating investigator will set the stimulation intensity between 15 and 20 mA according to individual tolerance. The intensity may subsequently be adjusted within this range if necessary to maintain a visible thumb flexion while remaining comfortable and well tolerated by the participant. Participants in the sham group will use an identical device with the same electrode placement, treatment duration, and operating procedures as those in the active MNS group. However, the device will be programmed to deliver 0 mA, thereby providing no electrical stimulation. This sham procedure was selected to control for the nonspecific effects associated with device application while avoiding unintended activation of the median nerve. Participants will be instructed not to modify the stimulation parameters independently. Any adjustment to the stimulation intensity will be performed only by the study investigator when clinically indicated.

Two self-adhesive surface electrodes will be placed over the right median nerve on the volar aspect of the forearm. The distal electrode (anode, +) will be positioned approximately 2 fingerbreadths proximal to the wrist crease, and the proximal electrode (cathode, −) will be positioned approximately 2 fingerbreadths proximal to the distal electrode along the course of the median nerve. Before the first treatment session, study personnel will verify correct electrode placement and provide standardized instructions regarding the intervention procedure. The stimulation site will be inspected before each treatment session for erythema, irritation, blistering, or other signs of skin injury.

Stimulation will be administered for 8 hours per day throughout the 2-week intervention period by trained study personnel. If mild skin irritation or discomfort occurs, the electrodes may be repositioned, and the stimulation intensity reduced while maintaining visible thumb flexion. Stimulation will be suspended if symptoms persist and permanently discontinued if a serious device-related adverse event (AE) or clinically significant intolerance occurs, as determined by the study investigator.

Treatment adherence will be monitored by study personnel and recorded in the CRF, including the daily stimulation duration, any interruptions, device-related problems, and AEs. Device function and electrode contact will be checked before each treatment session. If device malfunction occurs, stimulation will be stopped immediately, the malfunction will be documented, and the device will be inspected or replaced before treatment is resumed. If stimulation is interrupted because of medical procedures, clinical instability, technical problems, or other unavoidable circumstances, participants will resume stimulation as soon as clinically feasible on the same day to complete the planned 8-hour daily treatment whenever possible. Missed stimulation time will not be carried forward to subsequent days. All interruptions and their reasons will be documented and incorporated into the assessment of treatment adherence.

